### 2.6.2 KAP on type2 diabetes and its risk factors and complications of the disease:

A list of questions will be adopted from other generic tools to assess the level of knowledge among urban street food consumers on risk factors, prevention measures and complications of type2 diabetes ( Parmenter and Wardle, 1999; Shah, Kamdar and Shah, 2009; Barzegari *et al.*, 2011; Bano *et al.*, 2013; WHO, 2013; Mumu *et al.*, 2014; Ahmad and Ahmad, 2015; Fatema *et al.*, 2017; Yang *et al.*, 2017**)**. Another list of questions will be developed to capture information on positive and negative attitudes towards change in favour of reducing metabolic risk factors of type2 diabetes. The study also will assess the level of positive practice in relation to reducing the chance of developing metabolic risk factors of type2 diabetes.

2.6.3 Factors associated with adoption and compliance to the food plate mode: This study will also assess enabling factors (socio-economic, cultural and environmental factors) which in one way or another will influence adoption of plate model. This information will be collected from food vendors, consumers and other stakeholders (nutritionists, health environmental officers). This information will be collected using interview questionnaire and interview guide for FGDs and in-depth interview.

2.6.4 Effectiveness of intervention package in reducing type2 diabetes risk factors: At the end of an intervention the mean comparison using independent T-test of all metabolic risk factors for T2DM will be made between the control and intervention groups. For pre-post analysis, the study will apply Generalized Linear Mixed Models (GLMM) to accommodate fixed and random variables. Sensitivity analysis will be conducted to assess if variables which will be statistically significant by GLMM model, will be consistently significant using the Bayesian Modelling technique with Markov Chain Monte Carlo (MCMC). Post and baseline analysis will also employ both linear and logistic regression to assess the factors associated with both primary and secondary outcome of interest. The following are the metabolic risk factors which will be assessed: High Density Lipoprotein Cholesterol (HDL-C), Low Density Lipoprotein Cholesterol (LDL-C), Total Cholesterol (TC), and triglycerides Cholesterol (TG-C) Body mass index (BMI), Waist Hips Ratio (WHR) and Blood Pressure (BP) (4,5,22,23,47,49), these will be our primary outcome of interest. The study will also assess mean knowledge and attitude scores as our secondary outcomes, mean days of fruits/vegetable consumption per week, mean number of cigarettes smoked per week, drinks consumed per week and mean MET/week between the control and intervention sites. Frequency of alcohol consumption and smoking will be also compared between the control and intervention sites. Lastly, the study will also compare the proportion of quitting alcohol consumption and smoking tobacco products between the control and intervention sites.

2.6.5 Develop a model for predicting metabolic risk factors for type2 diabetes: After collecting the endline data then a model will be developed using Multivariate/Joint Bayesian techniques to assess socio-economic and behavirioal risk factors which influence each metabolic risk factors and those which influence these factors jointly. **Table 4** below shows the type of predictive/explanatory factors which will be modelled per each metabolic risk factor of T2DM(16).

Table 4 Dependent and independent variables

| **Dependent variables- Metabolic Risk factors of T2DM** | **Independent variables/confounders** |
| --- | --- |
| 1. Body Mass Index or Waist Circumference 2. Fasting Blood Glucose 3. High Density Lipoprotein 4. Triglyceride 5. Systolic BP 6. Diastolic BP | **Socio-economic and demographic risks:**  Marital status, Education, Ethnicity, Employment status, Sex and Age  **Lifestyle behaviours**  Family history of diabetes  Smoking: Never/previously/currently; Frequency of smoking  **Physical activities**  Interview methods will be used in measuring:  Type, frequency and intensity, Work-related, communing and leisure physical activities  **Dietary pattern:**  Vegetables, Fruits, Spreads and oil, Table salt & Alcohol consumption  **Others factors:**  Mean number of health plate consumed per week,  Type2 diabetes knowledge of vendors and consumers |

## 2.7 Implementation of intervention package (health education and plate model) and application of onehealth approach

2.7.1 Health education**:** To achieve the goals of this study, application of one health approach whereby different disciplines are involved in interdisciplinary manner to implement the project became inevitable. Participants will be educated on the behavioural, familial and metabolic risk factors for T2DM. The participants will also be educated on the prevention measures of T2DM. These measures will include recommended level of MET/Week of physical activities, recommended amount of alcohol to drink per week for each sex, the recommended amount of fruits and vegetable servings per day. In addition, the participants will be educated on the danger of smoking and eating excess fats, carbohydrate and fruits with high calories. The signs and symptoms of T2DM and complication of the diseases will be also explained to the participants. This part of intervention will be implemented by nurses working in diabetes clinic and providing dietary health education to diabetes patients. Nutritionist and health environmental officers will be part of the team since they work closely with the food vendors. If the findings from this study will be used to inform the food policy, guidelines and food systems, these officers will be responsible for monitoring compliance and adherence to the new changes.

2.7.2 Plate Model: Before implementing the food plate model the consumers and vendors who will consent to be recruited for the intervention arm will be educated on how to prepare the standard and recommended food plate model and its hypothesized role of reducing metabolic risk factors of T2DM. We envisaged that knowledge about the current topic will influence practice and increase uptake of an intervention. The benefits of serving the food plate model will be explained to the vendors and these benefits will include serving small amount of carbohydrate, getting extra business by selling separate portion of vegetables and fruits after the project implementation thus getting more profit. For the consumers the benefits of plate model will include paying reduced price for carbohydrate since amount to be served will be the quarter of the normal served amount. Other advantages will include preventing the consumers from excess weight gain and contributing to balancing lipid T2DM metabolic risk factors. More emphasize will be given to the participants regarding the recommended ratio of fruits, vegetables, fats/protein and carbohydrate. Participants will be also instructed on how to ensure that the food plate model contain the recommended amount of potassium, magnesium and calcium levels. The food plate model will consists of more fruits and vegetables which will be half normal eaten plate before the intervention and each quarter will comprise carbohydrate and fats/protein. The participants will be insisted to avoid diary with high saturated fats and cholesterol.

2.8 Project monitoring: To ensure sustainability of the outcomes; the project will involve municipals officers during the implementation of the study so that they take lead in promoting supply and consumption of healthy diet. Intervention program will take three months(57). Monitoring will be done to ensure adherence and compliance as per study protocol requirements. This will involve signing a daily healthy plate form and weekly visits (intervention arm) while a daily lunch form and weekly visit (control arm). The main targets indicators will include mean of metabolic components (systolic and diastolic blood pressure, fasting blood glucose, body mass index, waist circumference, triglycerides and high density lipoprotein), proportion of respondents with high knowledge and positive attitude before and after intervention.

2.9 Controlling bias and confounders: This project is prone to bias since food vendors will be responsible in identifying their regular customers a situation which is associated with selection bias, however, the vendors will be told that all identified clients will be approached to consent for the study. Interview bias which is associated with incomplete and inaccuracy data; this effect will be minimized by training data collectors and field supervision(58–62). This study is also prone to known and unknown confounders. Clusters randomization (market place), probability proportional to size allocation of vendors and multivariable analysis approaches will minimize confounding effects (58–62)**.**

2.10 Expected outcomes: The magnitude of type2 diabetes and its risk factors among consumers of urban street cooked food will be known. The level of knowledge and attitude on type2 diabetes and its risk factors among consumers and vendors of urban street cooked food will be known. Through this study the effects of health intervention (Health education and healthy eating plate model) on prevalence of metabolic risk factors of type 2 diabetes will be known. A model for monitoring and predicting metabolic risk factors of type 2 diabetes among consumers of urban street cooked food will be developed from this study. Consequently, the study findings will help to enhance and enrich the policy and guidelines for food regulatory authorities in Tanzania and elsewhere. Ultimately, the research findings will inform food policy and food related guidelines and will also help to improve food system in urban areas.

Table 5 Timeline and Milestones

| **Activity** | **Oct 2017-**  **Sept 2018** | | | | **Oct 2018-**  **Sept 2019** | | | | **Oct 2019-**  **Sept 20120** | | | |
| --- | --- | --- | --- | --- | --- | --- | --- | --- | --- | --- | --- | --- |
|  | **Q1** | **Q2** | **Q3** | **Q4** | **Q1** | **Q2** | **Q3** | **Q4** | **Q1** | **Q2** | **Q3** | **Q4** |
| 1. Writing proposal |  |  |  |  |  |  |  |  |  |  |  |  |
| 2.Application of Ethical Approval |  |  |  |  |  |  |  |  |  |  |  |  |
| 3. Attend monthly or quarterly supervisory meetings |  |  |  |  |  |  |  |  |  |  |  |  |
| 4.Attend at least 4 short courses & 5 conferences |  |  |  |  |  |  |  |  |  |  |  |  |
| 5.Write small proposals to mobilize l funds |  |  |  |  |  |  |  |  |  |  |  |  |
| 6. Write systematic review /meta analysis |  |  |  |  |  |  |  |  |  |  |  |  |
| 7.Site preparation |  |  |  |  |  |  |  |  |  |  |  |  |
| 8.Finalize protocol |  |  |  |  |  |  |  |  |  |  |  |  |
| 9.Supervisory and Mentorship |  |  |  |  |  |  |  |  |  |  |  |  |
| 10.Baseline data collection |  |  |  |  |  |  |  |  |  |  |  |  |
| 11.Implement intervention package |  |  |  |  |  |  |  |  |  |  |  |  |
| 12.Data management and analysis for baseline |  |  |  |  |  |  |  |  |  |  |  |  |
| 13.Defend Thesis |  |  |  |  |  |  |  |  |  |  |  |  |
| 14. End line data collection |  |  |  |  |  |  |  |  |  |  |  |  |

2.11 Ethical consideration: An ethical clearance will be sought from the Medical Research Coordination Committee of the National Institute for Medical Research. Regional and district authorities will be informed about the aim and procedures of the study. During the study, participants will be informed about the aims and benefits of the study and a written informed consent will be obtained from each participant. Names will not be used and confidentiality will be maintained by keeping data collection questionnaire locked in a secure cabinet, while the electronic data file will be kept in a password protected computer. Participants who will be examined and identified with hypertension, or diabetes (high blood sugar) will be referred to the nearest health facilities for further management. Those who will be screened and found with abnormal cholesterol and body mass index will be counselled and advised on proper approaches for risk prevention and control. This protocol will be registered in order to comply with WHO’s  [Helsinki](http://www.wma.net/en/30publications/10policies/b3/index.html) Declaration which states that "Every clinical trial must be registered in a publicly accessible database before recruitment of the first subject".

Table 6 Budget for the study project

| **S/No** | **Item** | **Description** | **Year1 (Euros)** | **Year2 (Euros)** | **Year3 (Euros)** | **Total (Euros)** | **Source** |
| --- | --- | --- | --- | --- | --- | --- | --- |
| 1 | Salary/Stipend | 36 months | 4,560 | 4,560 | 4,560 | **13,680** | ASPIRE |
| 2 | Tuition Fees |  | 5,200 | 5,121 | 5,120 | **15,442** | ASPIRE |
| 3 | Training / Workshop | Pm | - | - | - | **-** | Vliruos/others |
| 4 | Supervision | Lump sum | 381 | 381 | - | **762** | ASPIRE |
| 5 | Research cost (lab) | Lump sum | 19,650 | - | - | **19,650** | ASPIRE/others |
| 6 | Equipment(lab) | Lump sum | 762 | - | - | **762** | ASPIRE/others |
| 7 | Travel | Lump sum | 250 | 250 | - | **500** | ASPIRE |
| 8 | Miscellaneous | Lump sum | 300 | 300 | - | **600** | ASPIRE/others |
|  | **Total** |  | **31,103** | **10,612** | **9,680** | **51,396** |  |

|  | **Explanation/details** |
| --- | --- |
| 1 | Meal, Accommodation, fare |
| 2 | University fee and other costs including examination fee, medical costs, application fee, stationeries, book allowance, thesis production etc |
| 3 | Short courses, seminars and workshop |
| 4 | Supervision by academic supervisor |
| 5 | Salaries, car hire, reagents and supplies etc |
| 6 | Glucometer, scale, height body, tapes measure, BP machines |
| 7 | Bus ticket, tax charges and accommodation |
| 8 | All emergency expenses |

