# Operational definitions

**Metabolic risk factors of type2 diabetes:** Is the group of biological risks including high central obesity (Body Mass Index or waist circumference), blood glucose, reduced HDL, raised Triglycerides and raised blood pressure (1–3).

**Prevention package:** In this study this term “prevention package” includes health education (risk factors, prevention strategies and impact of the disease) and healthy food plate (recommended portion of carbohydrate, fruits, protein vegetables and cooking oils) (4,5).

**Street-vended foods:** Foods or beverages sold after being prepared on the street or at home and ready to eat or to be consumed immediately or later on the street/public places without further processing or preparation(6,7).

**Street food consumer:** Is a person who buys and eat foods or drink beverages prepared in the street or at home and sold in the streets/public areas (6,7).

**Regular street food client:** A person who consume at least three street vended lunches per week ***(to be operationalized and validated later)***

**Effectiveness of intervention:** refers to performance of an intervention in producing the intended outputs/outcomes

**Unhealthy diet**: Meals consumed in a day with less than two servings of fruits, less than five servings of vegetables, more than half plate of carbohydrate and protein(8).

**Unhealthy eating behaviours:** A practice of eating foods or drinks to feel full and satisfied without considering the amount of food or drink if it is appropriate or not (9)**.**

**Healthy food plate**: A plate that guides every person on healthy eating habits showing the recommended proportion and types of foods or drink that are to make up a healthy and balanced diet (4,5)**.**

**Components of Healthy plate:** Half meal vegetables and fruits, ¼ whole grains, ¼ proteins, cooked with healthy plant oils and drinking water(4,5)**.**

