# 2.0 Materials and Methodology

2.1 Study area: This study will be conducted in Dar es Salaam region. Dar es Salaam is the largestcity in Tanzania with land area of 538km^2^. It has five municipalities namely Ilala, Kinondoni, Temeke, Ubungo and Kigamboni. The region/city contributes about 80% of all national economy thus attracting more immigrants from inside and outside of the country for economic investments. The city is the third fastest-growing in Africa and the ninth fastest-growing in the world. According to the national census report of 2012 the population of Dar es Salaam was 4.36 million (41)**.** The population of the region is expected to over double up to 10.76 million by 2030(42). This study will be conducted in three already randomly selected districts and six market places (two per district). The selected districts are Ilala, Kinondoni and Ubungo. The region was considered for this study because of previous researches which indicated that majority of low and income people in the area consume street foods served by street vendors(26,27). The studies also indicated that the nutrition value of the foods supplied by street food vendors is questionable as they normally serve smaller amount of fruits and rarely served fruits due to limited capital and low knowledge on nutrition values of foods (26,27)**.** Such eating behaviours expose the consumers at risk of getting type2 diabetes due to increased risk of metabolic risk factors. In Dar es Salaam it was also observed that costs and attitude were the factors associated with low consumption of fruits and vegetables among pupils and student (27). Another study conducted in Dar es Salaam among HIV positive people indicated that consuming junk foods led to increased body weight which was perceived a strategy for increasing CD4 counts (43)**.**

2.2 Study population: Urban regular eaters of street cooked food, vendors and key stakeholders. Key stakeholders will include health environmental officers, municipal nutritional officers and officers from the national food regulatory authorities.

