2.3 Study design: This study will be intervention (experimental) with two arms control and experimental clusters. This design is appropriate for this study since it will allow researchers to measure the effects of an intervention package (health education and plate model) by comparing the outcomes of the package in the experimental group versus control group which will receive a placebo (health education) after three months of follow up. Healthy plate will contain ¼ carbohydrate, ¼ protein, ¼ vegetables and ¼ fruits. Health education will focus on risk factors of type2 diabetes, prevention strategies and complications of the disease and nutritional values of foods. A proposed intervention package will be assigned to the clusters (market places) randomly but subjects in the intervention sites will not be blinded in order to get the desired outcomes and justify the efficacy of an experiment. Before intervention, baseline information including behavioural risk factors (physical inactivity, unhealthy diet, and smoking, harmful alcohol consumption), metabolic risks (raised blood pressure, triglyceride, blood glucose, low HDL and central obesity) and socio-economic and familial risks (sex, age, income, location, knowledge, family history of diabetes) will be collected from both arms.After intervention the same information collected at the baseline will also be collected at the end line.

2.4 Sample size: The sample was calculated by considering the following statistical parameters: level of significance (Z_1-α_), power of the test (Z_1-β_), population standard deviation (δ) and population variance (δ^2^).The baseline indicator for the mean waist hips ratio of µ_0_ =0.82 and a target of reducing the mean of waist circumference by 5% after an intervention i.e. from 0.82 to µ_a_=0.78. A design effects (DE) of 1.5 to clear variance between clusters was applied and none response rate of 20%. With the above statistical parameters then an actual sample size is 278 (**Table 1**). This sample size will be doubled to include both arms (intervention and control). Furthermore, at least 50 food vendors will be recruited and each food vendor will be asked to identify their regular clients who will be approached for the study.

Sample size (n) calculation formula (44).

**
[figure not shown]
**

Table 1 Estimated sample size per each risk factor indicator

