| **S/No** | **Parameter** | **µ_o_** | **Δ** | **δ^2^** | **Desired % change in mean after 3 months** | **µ_a_** | **DE** | **Non response (20%)** | **N** |
| --- | --- | --- | --- | --- | --- | --- | --- | --- | --- |
| 1 | BMI(Kg/m^2^) | 22.9 | 4.6 | 21.2 | 5 | 21.8 | 1.5 | 0.8 | 204 |
| 2 | TC(mmol/L) | 4.6 | 0.78 | 0.6 | 5 | 4.4 | 1.5 | 0.8 | 178 |
| 3 | TG(mmol/L)* | 1.7 | 1.1 | 1.2 | 12 | 1.5 | 1.5 | 0.8 | 353 |
| 4 | SBP (mmHg) | 129 | 21.3 | 453.7 | 5 | 122.2 | 1.5 | 0.8 | 129 |
| 5 | DBP (mmHg) | 80.3 | 12.2 | 148.8 | 5 | 76.3 | 1.5 | 0.8 | 109 |
| 6 | FBG(mmol/L) | 4.8 | 1.6 | 2.6 | 10 | 4.3 | 1.5 | 0.8 | 120 |
| 7 | WHR (none) | 0.82 | 0.2 | 0.0 | 5 | 0.779 | 1.5 | 0.8 | 278 |

***Source:*** (14)

2.5 Sampling procedures: This study will also apply a multistage cluster sampling whereby; three out of five districts have been selected randomly from Dar es Salaam region. Thereafter, mapping of market places (clusters) will be done and in each selected district two market places will be randomly selected then randomized one to receive an intervention package (health education and plate model) and another to receive a placebo (health education) . The step will be followed by mapping of food vendors to identify eligible food vendors and form a sampling frame per each cluster. Thereafter, probability proportion to size will be done to determine the number of vendors to be recruited per each cluster. Food vendors will be also selected randomly from each cluster to participate in the study. Each selected food vendor will identify regular customers then consent to participate in the trial will be sought from all identified clients (**Table 2**).

Table 2 Summary for sampling procedure

| **Stage** | **Ilala** | **Ubungo** | **Kinondoni** |
| --- | --- | --- | --- |
| 1. Identify the market places(MP)/clusters | 5 | 9 | 8 |
| 2. Identify and match eligible MPs | 5 | 9 | 8 |
| 3. Select randomly the required number of MPs for the study | 2 | 2 | 2 |
| 4. Assign MPs randomly into control and intervention arms | 2 | 2 | 2 |
| 5. Mapping Food vendors(FVs) | xx | Xx | Xx |
| 6. Identify eligible FVs | xx | Xx | Xx |
| 7. Use probability proportion to size (PPS) to allocate ≥50 FVs | xx | Xx | Xx |
| 8. Mapping of eligible* regular clients per FV | xx | Xx | Xx |
| 9. Seek consent and recruits all regular clients /FV | xx | Xx | Xx |

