|  | 1. Others (specify)___________________________ | |  | Qn40l |
| 41. | **Mention at least five complications of type2 diabetes** | |  |  |
|  | 1. Amputation | |  | Qn41a |
|  | 1. Stroke | |  | Qn41b |
|  | 1. Kidney failure | |  | Qn41c |
|  | 1. Blindness | |  | Qn41d |
|  | 1. Impotence | |  | Qn41e |
|  | 1. Nerve damage | |  | Qn41f |
|  | 1. Heart attacks | |  | Qn41g |
|  | 1. Others (specify)_____________________ | |  | Qn41h |
| **Nutritional values** | | | | |
| 42. | What is the best composition of portion of carbohydrate, fruits, vegetables and proteins healthy food plate?  1) ¼ Carbohydrate, ¼ Protein, ½ Fruits and vegetables, Water/milk  2) DK  3) Others_______________ | |  | Qn42 |
| 43. | Do you think health experts recommend that people should be eating more, the same amount, or less of these foods? (Tick one box per food) | |  |  |
|  | **Food** | | **1.More**  **2.Same**  **3.Less**  **4.Not sure** |  |
|  | a) Vegetables | |  | Qn43a |
|  | b) Sugary foods | |  | Qn43b |
|  | c) Meat | |  | Qn43c |
|  | d) Starchy foods | |  | Qn43d |
|  | e) Fatty foods | |  | Qn43e |
|  | f) High fibre foods | |  | Qn43f |
|  | g) Fruit | |  | Qn43g |
|  | h) Salty foods | |  | Qn43h |
| 44. | How many servings of fruit and vegetables a day do you think experts are advising people to eat? (One serving could be, for example, an apple or a handful of chopped carrots)   1. Fruits _______________   b) Vegetable_______________ | |  | Qn44 |
| 45. | Saturated fats are mainly found in:(tick one)  1.Vegetable oils  2. Dairy products  3. Both (a) and  4. Not sure | |  | Qn45 |
| 46. | If a person wanted to reduce the amount of salt in their diet, which would be the best choice? (tick one)  1.Buy food with already added salts like sausages, manufacture beefs, chips crips etc  2. Add salt during cooking himself/herelf  3. Not sure | |  | Qn46 |
| 47. | Are you aware of the major non-communicable disease which is related to how much salt or sodium people eat?   1. Yes 2. No 3. Not sure | |  | Qn47 |
| 48 | If yes, which non-communicable disease do you think is related to salt?   1. High blood pressure 2. Not remember 3. Other______________________ | |  | Qn48 |
| 49. | Are you aware of any major non-communicable diseases that are related to a low intake of fruit and vegetables?   1. Yes 2. No 3. Not sure | |  | Qn49 |

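### The protocol fixes the carbohydrate in the experimental plate in two ways that cannot both be followed: a quarter of the plate, and a quarter of the usual serving

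*Protocol*

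**What the plan says.** The composition of the plate appears in five places in the protocol.

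- Operational definitions: "Half meal vegetables and fruits, ¼ whole grains, ¼ proteins, cooked with healthy plant oils and drinking water".
- Section 2.3, Study design: "Healthy plate will contain ¼ carbohydrate, ¼ protein, ¼ vegetables and ¼ fruits".
- Section 2.7.2, Plate Model, among the benefits explained to consumers: "paying reduced price for carbohydrate since amount to be served will be the quarter of the normal served amount".
- Section 2.7.2, later in the same paragraph: fruit and vegetables are to make up half of the plate as normally eaten before the intervention, and "each quarter will comprise carbohydrate and fats/protein".
- Appendix B, Qn42, the first response option, which matches the protocol's healthy plate: "¼ Carbohydrate, ¼ Protein, ½ Fruits and vegetables, Water/milk".

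Section 2.5 makes the plate the planned difference between the arms. In each of three districts two markets are drawn, then "randomized one to receive an intervention package (health education and plate model) and another to receive a placebo (health education"). That gives three intervention markets.

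Plates are counted in three places: a daily healthy plate form (section 2.8), the endline item Qn132, and the weekly mean number of plates as an explanatory variable in Table 4. Neither section 2.8, Qn132 nor Table 4 says which plate qualifies.

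**The concern.** Both arms are to receive health education, so what a vendor puts on the plate is the experimental treatment. A share of the plate and a fraction of the customary serving are different quantities, and a vendor who follows one will generally not meet the other. Section 2.8 promises to monitor adherence to the protocol's requirements, but on carbohydrate those requirements conflict.

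The delivered dose could therefore differ between vendors and markets without anyone departing from the text. The plate counts used for adherence and for the prediction model could mix plates made to different rules, and a later user of the results could not tell which plate had been tested.

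**Working it through.** There is no stated sample size, power or error rate to reproduce here. The check compares the two carbohydrate rules and then the fruit and vegetable rules.

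**Carbohydrate.** Let *c* be the share of the usual plate filled by carbohydrate, and keep the plate size unchanged.

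- Rule A (section 2.3, the composition sentence of 2.7.2, Qn42, and the Operational definitions as whole grains): carbohydrate = 0.25 of the plate. As a fraction of the usual serving this is 0.25 / *c*.
- Rule B (the benefit sentence of 2.7.2): carbohydrate = 0.25 × *c* of the plate. As a fraction of the usual serving this is 0.25.
- Ratio A to B = 0.25 / (0.25 × *c*) = 1 / *c*. The rules agree only at *c* = 1.

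The protocol gives no value for *c*. Section 1.1 says only that Tanzanian street food carries large portions of both carbohydrate and protein, which is not compatible with *c* = 1. The working range is 0.50 to 0.75, with 0.40 and 1.00 shown as outer values.

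| Assumed *c* | Rule A, share of plate | Rule B, share of plate | Ratio A/B | Rule A as fraction of usual serving |
|---|---|---|---|---|
| 0.40 | 25% | 10.0% | 2.50 | 62.5% |
| 0.50 | 25% | 12.5% | 2.00 | 50.0% |
| 0.60 | 25% | 15.0% | 1.67 | 41.7% |
| 0.75 | 25% | 18.8% | 1.33 | 33.3% |
| 1.00 | 25% | 25.0% | 1.00 | 25.0% |

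At *c* = 0.50, rule A halves the usual carbohydrate serving and rule B cuts it by 75%. Over 0.50 to 0.75, the rule B portion is 50% to 25% smaller than the rule A portion.

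**Plate size.** If the new plate were *s* times the size of the usual one, rule A would give 0.25 × *s* and rule B 0.25 × *c*, so a plate shrunk to *s* = *c* would satisfy both. The composition sentence in 2.7.2 does not fit that reading, because it sizes the fruit and vegetable half against the plate eaten before the intervention. That points to *s* = 1.

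**Fruit and vegetables (secondary).** Section 2.3 requires 1/4 + 1/4. The Operational definitions, 2.7.2 and Qn42 require a total of 1/2. A plate with 3/8 vegetables and 1/8 fruit totals 4/8 = 1/2, so it meets the combined rule and fails section 2.3. Every plate that meets section 2.3 also meets the combined rule. Section 2.3 is therefore the stricter version and is compatible with the others.

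**The case against.** The strongest reply is that four of the five places agree on the broad shape of a quarter, a quarter and a half. The odd sentence concerns benefits and price, and may be a clumsy way of saying a quarter of the plate as normally served. That is a plausible account of how it arose. But the sentence states the amount to be served, sits in the implementation section, and is to be given to consumers as the reason they will pay less. It needs correcting or confirming.

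Several stronger readings are tempting, and the documents do not support them.

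- A reader might infer that there are several mutually incompatible plates. Only the carbohydrate rules conflict. The fruit rule differs in strictness, and the other differences (whole grains or any carbohydrate, protein or fats/protein, water or water/milk) are loose wording with no demonstrated effect.
- A reader might infer that a plate with no fruit counts as healthy under the combined rule, and that this is the usual case because section 2.1 says of vendors that "they normally serve smaller amount of fruits and rarely served fruits due to limited capital". The combined rule names both foods, so a plate without fruit does not plainly meet it. Section 2.1 describes practice before the intervention, whereas enrolled vendors must be ready to implement the model (Table 3) and are trained to prepare the plate (2.7.2).
- A reader might infer that vendors will deliver and count different plates. The text permits this but does not show it, and training may bring practice together. The daily form's layout is not in the pages available, so it may already carry a definition.
- A reader might infer that the main result is compromised. Section 2.6.4 compares metabolic means between the randomised groups and uses no plate counts.

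**Conclusion.** The carbohydrate contradiction stands. It is in current text, partly within a single paragraph, and on a plate of unchanged size it holds for any usual carbohydrate share below 100%. Its size depends on that share: 12.5% to 18.8% of the plate against 25%, for an assumed usual share of 0.50 to 0.75. The unequal split of fruit and vegetables is a real but lesser point.

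The consequence is that dose and plate counts can vary between vendors and across the three intervention markets. This weakens treatment fidelity, the meaning of Qn132 and of the Table 4 predictor, and the reproducibility of the package. It does not by itself bias the randomised comparison of means. It should be fixed, and is best settled before vendors are trained, because plate counts collected under mixed rules cannot be re-scored afterwards unless the components were recorded.

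**What to change.** Reconcile the Operational definitions, section 2.3, both sentences in section 2.7.2 and the Qn42 key into one plate specification of the sponsor's choosing. State the reference quantity for each share, for example whether it is a fraction of the plate as served, of the plate usually eaten, or of the usual serving of that food. Say whether fruit and vegetables have separate shares or a joint one. Use that definition unchanged in vendor training, on the daily healthy plate form and for Qn132, so that the Table 4 predictor counts one thing. Which composition is right is for the sponsor and its nutrition advisers, and this review takes no position on it.

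The cost is minor wording in the protocol, the training text, the form and the questionnaire. A single explicit definition may also lower the reported number of healthy plates.
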